#### Adverse events of acupuncture

2.10.5

The incidence rate of acupuncture's AEs during treatment will be counted. Clinical symptoms and related laboratory examination results of acupuncture's AEs will be recorded to judge their grades. Follow-up visits after AEs will be recorded.

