### Sample size

2.13

Based on the RCT report published by Jiang et al^[43]^ in 2016, the sample size was estimated with MoCA as the main outcome. After 12 weeks of treatment, the difference of MoCA between pre-therapy and posttherapy in the conventional rehabilitation group (without acupuncture) was 2.83 ± 1.13, and that of MoCA between pre-therapy and posttherapy in acupuncture group was 1.33 ± 1.20. The test level was set at *α* = 0.05 and *β* = 0.1. By comparing the differences between 2 independent samples, PASS 2008 software was used to calculate that the required sample size of each group was 13 cases, and 26 cases in both groups.

To sum up, considering that the follow-up loss rate is 20%, the sample size should be 26/(1 – 0.2) = 33 cases. Considering that we have enough research capacity to fulfill the expected research tasks, we intend to expand the sample size to a total of 50 cases, 25 cases in each group.

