### Randomization and allocation concealment

2.14

The stratified random allocation operation of experimental group and control group will be completed by the researcher of the Clinical Research Center, South China Research Center for Acupuncture and Moxibustion, Guangzhou University of Chinese Medicine. The programming and randomized operation will be performed by PROC PLAN of SAS 9.2. The results of random allocation will be distributed through the central random allocation system in the internet.

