### Statistical analysis

2.19

The statistical tests involved in this study will include unilateral and bilateral tests with a significance level of alpha = 0.05. Statistical analysis will be completed by SPSS 22.0 software (International Business Machines Corp., Armonk NY).

Effect analysis will involve a population consisting of per-protocol subject analysis and intention-to-treat analysis. We will adopt a repeated measures design approach to compare the treatment outcomes (MoCA, MMSE, and ADAS-cog) over time between 2 groups. The model will be built to distinguish the intervention effect and the time effect. Among-group differences at each assess time point will be further tested by student *t* test. Categorical variables, containing categorical baseline variables and incidence of AEs, will be analyzed by a chi-square (χ^2^) or Fisher exact test.

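### Adverse-event incidence is compared between arms only by a chi-square or Fisher test at 25 per arm, which says little about safety; per-arm rates and a risk difference with confidence intervals would say more (minor)

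*Protocol article*

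**What the plan says.** Section 2.19 (Statistical analysis) fixes one method for two kinds of data: "Categorical variables, containing categorical baseline variables and incidence of AEs, will be analyzed by a chi-square" or Fisher exact test. It gives no rule for choosing between the two. The tests in the study "will include unilateral and bilateral tests" "with a significance level of alpha = 0.05", and neither sidedness is tied to a particular analysis. For the scales analysed over time, the section adds: "Among-group differences at each assess time point will be further tested by student" *t* test.

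Section 2.13 sizes the trial on MoCA and then enlarges it: "we intend to expand the sample size to a total of 50 cases, 25 cases in each group". Section 2.14 describes stratified randomisation and says: "The results of random allocation will be distributed through the central random allocation system in the internet".

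On adverse events (AEs), section 2.10.5 says that the incidence of acupuncture "AEs during treatment will be counted", with grading and follow-up recorded. Section 2.17 has timing, symptoms, duration, severity and treatment entered in the case report forms, and promises an analysis of the impact of all AEs at the end, without naming a method. The abstract and introduction name safety as an aim of the pilot and say that it should inform a larger trial.

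**The concern.** The between-arm comparison of AE incidence rests on a p-value from a trial that was not sized for it. With 25 per arm, a test at 0.05 will usually miss an excess that matters, so a non-significant result cannot separate no excess from too few patients to see one. The next trial needs the AE rate in each arm and the uncertainty of the difference. The only method that section 2.19 names for AEs gives neither.

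The verdict can also turn on choices left open. Chi-square or Fisher, one-sided or two-sided, can put the same table on either side of 0.05.

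A smaller point sits in the same sentence. Testing categorical baseline variables asks whether a difference arose by chance, when random allocation has already settled that it did.

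**Working it through.** **Inputs.** 25 per arm (section 2.13); alpha 0.05, chi-square or Fisher, sidedness unassigned (section 2.19). The protocol gives no AE rates, so the rates and counts below are assumptions for illustration.

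**The plan's own figure.** The only sample-size calculation is for MoCA. With a difference of 2.83 − 1.33 = 1.50, a pooled SD of √((1.13² + 1.20²)/2) = 1.1655, two-sided alpha 0.05 and power 0.90:

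n = 2 × (1.960 + 1.282)² × (1.1655/1.50)² = 12.69, so 13 per group.

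This reproduces the stated 13, and 26/0.8 = 32.5 reproduces the stated 33. No AE figure enters the calculation.

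**Step 1: p-values for 5/25 v 0/25.**

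- One-sided Fisher: C(25,5)/C(50,5) = 53,130/2,118,760 = 0.0251.
- Two-sided Fisher: 2 × 0.02508 = 0.0502.
- Uncorrected chi-square: 5.56 on 1 df, p = 0.018.
- Yates-corrected chi-square: p = 0.059.

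The smallest expected count is 2.5. Neighbouring tables, two-sided Fisher: 4 v 0 gives 0.110 and 6 v 0 gives 0.022. So 5 v 0 sits on the edge.

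**Step 2: power of the two-sided Fisher test.** Sum Bin(a; 25, p₁) × Bin(b; 25, p₂) over all pairs (a, b) with Fisher p ≤ 0.05.

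| Assumed true rates | Exact power |
|---|---|
| 20% v 0% | 38% |
| 20% v 2% | 30% |
| 20% v 4% | 23% |
| 20% v 5% | 20% |
| 30% v 5% | 55% |

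For 20% v 0% this is the chance of at least 6 events in 25, because 5 v 0 just fails. Over the four 20% rows, a true excess of 15 to 20 points is missed in 62% to 80% of trials.

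**Step 3: what intervals would show.**

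- 5/25: 20%, exact 95% CI 6.8% to 40.7%.
- 0/25: 0%, exact upper limit 1 − 0.025^(1/25) = 13.7%.
- Risk difference, Newcombe. The Wilson limits are 8.86% to 39.13% for 5/25 and 0% to 13.32% for 0/25. Lower limit: 0.20 − √((0.20 − 0.0886)² + 0.1332²) = 0.026. Upper limit: 0.20 + (0.3913 − 0.20) = 0.391. The difference is 20 points, 95% CI 2.6 to 39.1.

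**Step 4: interval beside a p-value.** At 6 v 1, Newcombe gives 0.05 to 39.7 points and Fisher p = 0.098. At 8 v 2, it gives 1.5 to 44.4 points and Fisher p = 0.074. In both, as at 5 v 0, the interval excludes zero while two-sided Fisher exceeds 0.05. Printing both would give conflicting messages, so the fix should leave out the test.

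**Step 5: baseline.** Under sound randomisation the null holds by design, so every rejection is a false alarm and a large p does not show balance. For example, 12/25 v 6/25 (48% v 24%) gives two-sided Fisher p = 0.14.

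**The case against.** **AE reporting is wider than one test.** Sections 2.10.5 and 2.17 commit to counting, grading and documenting AEs. This stands: the pilot will have AE counts. What is missing is any comparison of the arms other than a test.

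**The harm is inferred.** A reader might conclude that the plan will declare the arms equally safe, or the groups balanced, whenever p exceeds 0.05. No section says so, and no baseline p-value is used to choose covariates or alter an analysis. The risk lies in how such results tend to be read.

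**The 5 v 0 example is fragile.** It is non-significant with two-sided Fisher or the Yates correction, and significant with one-sided Fisher or uncorrected chi-square. Chi-square or Fisher is also common shorthand for a rule based on expected counts, which would select Fisher here. Both remarks are fair. The case rests on the power figures, and the example only shows how close the verdict can be.

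**Low power comes from the sample size.** True, and an interval from the same data will be wide. But a wide interval shows how much excess remains possible, whereas a bare non-significant p-value hides it.

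**A high false-alarm rate at baseline cannot be claimed.** Five to ten independent tests at a true 5% would give 23% to 40% (1 − 0.95⁵ and 1 − 0.95¹⁰). Fisher's actual size at 25 per arm is only 2.2% to 3.3% for common rates of 20% to 50%, and the protocol does not give the number of baseline tests. That range should not be used.

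**The per-time-point t tests need not include baseline.** Section 2.1 and Table 1 list baseline as an assessment, but the sentence follows the comparison of treatment outcomes over time and may mean post-treatment visits only. It is ambiguous wording, not a clear commitment to test at baseline.

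**An analysis plan may add intervals.** It may. The point is that the method stated here is a poor choice, whatever is added elsewhere.

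**Conclusion.** The point holds as a minor one. Section 2.19 fixes a significance test as the between-arm analysis of AE incidence in a trial sized on MoCA alone. With 25 per arm, two-sided Fisher power is 23% for 20% v 4% and 38% for 20% v 0%, so a non-significant result says little about safety. The figures assume those AE rates, all 25 per arm analysed, and a two-sided test; fewer analysed patients would generally lower the power.

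The baseline tests are a secondary matter. They are uninformative under randomisation, but removing them changes no trial estimate. The quoted sentence covers categorical baseline variables only. Neither the MoCA comparison nor the feasibility criteria in Table 3 are affected.

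**What to change.** In section 2.19:

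1. For AEs, report the number and percentage of participants with at least one AE in each arm with an exact 95% CI, and the risk difference with a 95% CI by a named method such as Newcombe. Base the safety statement on these intervals, with no significance test.
2. As a minor addition, delete the tests on categorical baseline variables, present baseline by arm descriptively, and state that the per-time-point *t* tests apply to post-baseline visits only.

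The cost is wording alone; no new data, patients or procedures are needed. The downside is that the safety statement will show wide intervals. Even no events in an arm of 25 leaves rates up to 13.7% possible.

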### Handling of missing data

2.20

If the missing value is less than 5%, a full case analysis without calculating missing date will be adopted. If the missing value exceeds 5%, Little test will be adopted. If Little test showed that the full case data set is a random sample, the full cases without calculating missing date will be continued analyzing. If Little test showed that the full case data set is not a random sample, the point estimation and 95% confidence interval will be reported, with a worst- and best-case scenario imputation for the missing date. If the worst- and best-case analysis reach the same conclusion, we will not carry out multiple imputations. Or else, under the assumption of randomly missing value, multiple imputations will generate 10 estimated data sets. The pooled intervention effect and 95% confidence interval of the analysis of every data set after multiple imputation will constitute the results of the trial.

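### Above 5% missing data, a non-significant Little test is taken to show that complete cases are a random sample, and no sensitivity analysis is named on that branch

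*Protocol article*

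**What the plan says.** Section 2.20 of the protocol article sets out a decision chain.

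- Little missing data: "If the missing value is less than 5%, a full case analysis without calculating missing date will be adopted".
- More missing data: "If the missing value exceeds 5%, Little test will be adopted".
- Test does not reject: "If Little test showed that the full case data set is a random sample, the full cases without calculating missing date will be continued". Nothing else is attached to this branch.
- Test rejects: a point estimate and 95% interval are reported "with a worst- and best-case scenario imputation for the missing date". Multiple imputation (10 data sets) follows only if the two extreme scenarios lead to different conclusions.

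Section 2.19 says "Effect analysis will involve a population consisting of per-protocol subject analysis and intention-to-treat analysis". It plans a repeated-measures comparison of MoCA, MMSE and ADAS-cog, with t tests at each visit. Section 2.13 sizes the trial "considering that the follow-up loss rate is 20" per cent. Table 1 has MoCA at baseline, week 12, and 3 and 6 months after treatment, with none between baseline and week 12.

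**The concern.** The rule turns absence of evidence into a positive finding. Little's test compares the observed means of groups with different missing-data patterns. Failure to reject can mean that loss is unrelated to scores. It can also mean that the trial is too small to tell, or that loss depends on scores nobody recorded. In a trial of 50 the last two are serious possibilities, and on this branch the plan names nothing that would reveal them.

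The pattern that biases a treatment contrast is loss that depends on response differently in the two arms. The article gives reasons to consider it. The Discussion expects that compliance may be limited and that some participants may guess their arm. Section 2.17 has participants stop treatment after an undesirable effect, and only one arm has needles inserted. The pilot's efficacy estimate is meant to inform a larger trial, so a distorted estimate could mislead that decision.

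**Working it through.** **1. The plan's own figures.** Section 2.13 gives changes of 2.83 (SD 1.13) and 1.33 (SD 1.20), with "The test level was set at *α* = 0.05 and *β* = 0.1". Only the size of the difference is used here.

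- Difference: 2.83 − 1.33 = 1.50. Mean variance: (1.13² + 1.20²)/2 = 1.358.
- n per group = 2 × (1.960 + 1.282)² × 1.358 / 1.50² = 12.7, so 13. Total 26, and 26/0.8 = 32.5, so 33.

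Both match the plan with a two-sided test. The 1.5 points serve below as a yardstick.

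**2. Is the test reached?** 5% of 50 is 2.5, so below 5% means at most 2 participants lost. With 20% loss:

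P(X ≤ 2) = 0.8⁵⁰ + 50 × 0.2 × 0.8⁴⁹ + 1225 × 0.2² × 0.8⁴⁸ = 0.00001 + 0.00018 + 0.00109 = 0.0013.

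This counts participants. If MoCA values are counted, 10 people missing only month 6 give 10/(50 × 4) = 5%, exactly on the boundary, which the rule assigns to neither side.

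**3. Can the test see a baseline difference?** With 10 lost and 40 kept, SE = √(1/10 + 1/40) = 0.354 SD.

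- Shift of 0.5 SD: 0.5/0.354 = 1.41; two-sided power at 5% is 28% (t) or 29% (normal).
- Shift of 0.8 SD: 0.8/0.354 = 2.26; power is 60% (t) or 62% (normal).

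**4. Bias when loss depends on response.** Simulation assumptions, not in the documents: 25 per arm, no true effect, baseline/week-12 correlation 0.7, change SD 1.17, about 20% to 23% lost after week 12, log-odds of loss 1.2 per SD of response, test pooled over arms, listwise deletion, 4,000 to 6,000 trials per scenario. Ranges are over repeated runs; bias is absolute.

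| Who tends to leave | Little test rejects | Complete-case bias (points) | Type I error |
|---|---|---|---|
| Poor responders, sham arm only | 24–26% | 0.25–0.27 | 10–11% |
| Opposite dependence in the two arms | 6% | 0.50–0.53 | 29–31% |
| Either, all observed week-12 scores used | – | about 0 | about 5% |

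As a share of 1.5 points: 0.25/1.5 = 17% and 0.53/1.5 = 35%. Among trials that pass the test, bias was no smaller (0.27 and 0.52–0.53), so passing gives no protection.

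**5. Loss during treatment.** A second simulation removed every post-baseline score of those lost (20% per arm, baseline SD 2.0, change SD 1.2, correlation 0.7 between changes, 600 trials per scenario). The test rejected in 3.5% to 4% of trials, no more than its nominal 5%. Bias was 0.26 points (selection in one arm; type I error 13%) and 0.54 points (opposite selection; 37%). At 12% loss, bias was 0.18 to 0.35 points and type I error 9% to 20%. Unequal loss alone (2 versus 8 of 25, unrelated to outcome) gave bias of about −0.01 to −0.02 and type I error of about 5%.

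**6. Does a missing-at-random analysis repair loss before week 12?** Only baseline is then observed. With the step 4 parameters, week-12 scores regressed on arm and baseline still carry a bias of 0.19 to 0.23 points (sham only; type I error 9–10%) and 0.40 to 0.46 (opposite selection; 23–28%). In one matched set these compare with complete-case biases of 0.23 and 0.46, so 0.19/0.23 = 83% and 0.40/0.46 = 87% of the bias remains.

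**The case against.** Several stronger readings are tempting, and the article does not support them.

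- **That the test pools the arms.** Section 2.20 is silent. Run by arm at 0.025 each, it rejects in about 47% to 52% of trials in the opposite-selection case with loss after week 12, not 6%. That still lets about half through. For loss during treatment, adding arm to the test did not help (about 1% rejection).
- **That observed week-12 scores will certainly be discarded.** The visit-by-visit t tests and the unspecified repeated-measures model in section 2.19 could use every score at week 12, and the wording in section 2.20 may mean only that nothing is imputed. Listwise deletion is one reading.
- **That the rule contradicts intention to treat.** Section 2.19 names that analysis without saying how missing outcomes enter it, and an analysis plan may. This is a tension, not a contradiction.
- **That only extreme-case estimates remain after rejection.** The text also mentions a point estimate and interval.
- **That unequal drop-out biases the result.** By itself it does not (step 5).
- **That a mixed model cures the problem.** It does so only for loss after week 12 that depends on observed scores. The article does not say when the 20% is lost, and Table 3 tracks drop-out during treatment.

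This is also a feasibility pilot, so efficacy error rates matter less than in a confirmatory trial. That limits the stakes but does not remove them, because the abstract also gives the pilot an efficacy purpose. None of these points defends reading non-rejection as proof.

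**Conclusion.** The point holds for the decision rule itself, which section 2.20 fixes and does not leave to another document. A non-significant Little test in 50 people cannot show that complete cases are a random sample, yet the plan then stops, with no sensitivity analysis named. That the test is reached is near certain if participants are counted and 20% are lost. Its low power follows from 10 against 40, and its blindness to unobserved scores is a property of the method.

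The size of the harm is conditional. It needs drop-out that depends on response differently by arm. Under moderate assumed selection, a pooled test and listwise deletion, the bias is about 0.25 to 0.53 MoCA points and type I error about 10% to 31%. Weaker selection would give less. The change should be made; it does not call the design into question.

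**What to change.** Remove the 5% threshold and the Little-test condition from section 2.20. State that the primary intention-to-treat analysis is a likelihood-based linear mixed model on all observed MoCA scores of all randomised participants, with group, visit, group-by-visit interaction, baseline MoCA and the stratification factor (MIXED in the SPSS package already named). Always report multiple imputation by arm and the best-/worst-case analyses as sensitivity analyses, whatever Little's test shows.

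The text should add that, for people lost during treatment, only baseline is available. The model and the imputation then cannot remove most of the bias from response-related loss, and the best-/worst-case analyses are there to show how far the conclusion depends on it.

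Cost: revised wording and slightly more analysis work. No new data are needed.

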### Quality control

2.21

Before the experiment, all subjects participating in this study will receive the same training, detailed description of the study operation process, explanation of acupuncture related knowledge, and examination characteristics of ERP P300, MRI, and fMRI. All assessment will be conducted by a team led by a qualified professional evaluator. Researchers who participate in efficacy evaluation must have a certificate of medical practitioner and will not take part in the treatment of participants. All researchers will be trained and assessed by acupuncture physicians above the associate chief physician on standard operating procedure (including all kinds of questionnaire application methods, acupuncture methods, etc). In each research center, participants will be fixed as the same acupuncturist to perform the operation. Special independent supervisors will be set up in each research center. Each participant will be given a medication history book. The researchers will instruct participants to keep detailed records of all specific participant conditions during the study, including drug name, drug dosage, time of taking drug, and possible symptoms after taking drug. All data are entered into the data management system.

## Discussion

3

Acupuncture therapy has been used in China for more than 2000 years^[44]^ and has been generally practiced in Western countries in recent years.^[45]^ Recently, despite some evidence of acupuncture for aMCI emerging, methodological quality is generally not high enough to produce convincing and suggestive results. We design a rigorous RCT, using the control group method to decline bias of test and ensure the dependability of the RCT. And the study is a significant RCT aimed to treat aMCI.

This RCT has some improvement compared with previous trials. Firstly, it is a problem for the acupuncture investigators how to select the acupuncture points.^[46]^ According to our in-depth study on aMCI and experience of acupuncture, Tongdu Tiaoshen Acupuncture, namely Baihui (GV20), Dazhui (GV14), and bilateral Ganshu (BL18), and Shenshu (BL23) will be used as therapeutic acupoints. Secondly, we select the MoCA as the primary outcome. Multiple guidelines^[27,47]^ suggest the MoCA as the primary outcome of aMCI, and many aMCI studies adopted the MoCA as an assessment outcome. Finally, we have set a control group to realistically examine recruitment, randomly allocation, complement of interventions, and blinding evaluation.^[48]^ Nowadays, placebo contrast for acupuncture contains non-acupoint, superficial, and sham acupuncture.^[49–51]^ Some people think efficacy of acupuncture is controversial, as acupuncture takes effect primarily by a placebo result, or the controls of sham acupuncture maybe not absolutely non-effective.^[52–54]^ In the study, control group will accept sham acupuncture, whose needles will not insert into the skin. In each group, Park Sham Device will be used, and the acupoints are same. The designs will help reduce non-specific influence in the sham acupuncture group. Besides, acupuncture venue is a separate closed-door treatment room. Only the acupuncturists and a subject will be present at the same time to ensure that different subjects will not guess the way of needling received by each other.

Nevertheless, the study still faces some challenges. Firstly, the screening criteria for subjects in this study are very strict to ensure the homogeneity of subjects’ baseline and the validity of test results. Therefore, it may not be possible to recruit a large number of eligible subjects in a short period of time. We will summarize the experience after preliminary test, so as to expand the sample size and carry out the formal experiment in the next stage. Secondly, it is almost impossible to implement blind method for acupuncturists and it is inevitable that acupuncturists will know the treatment. Thirdly, in China, especially in Guangdong, many elderly people have received acupuncture treatment and know the feeling of being needled, so it is not easy to blind the subjects in the study. Some subjects may guess whether they are receiving real acupuncture treatment or not. To ensure the smooth implementation of blinding, participants in the 2 groups will use Park Sham Device when receiving acupuncture, and all participants are required to close their eyes during the whole course of treatment. In order to standardize the use of these false needle devices, all acupuncturists participating in the treatment will receive unified training and assessment before the start of the study, so as to ensure the consistency of the needle manipulation process and stimulation intensity. Fourthly, subjects will spend a lot of time on treatment because each treatment takes at least 1 hour and lasts for 12 weeks. Therefore, we anticipate that the compliance of subjects may not be high enough. In order to improve the compliance of subjects, we keep in touch with the subjects and at least 1 family member of the subjects. Let them realize the importance of intervening in aMCI by explaining the relationship between aMCI and AD in detail. In addition to the subjects, we will inform the family members of the research process in detail, so that the family members would urge the subjects to complete the treatment process. Meanwhile, we will give some compensation incentives to the participants.

In order to reach our goals, we will try to make every step standard, such as selection of acupoints, manipulation of acupuncture, needle apparatus, and needle apparatus’ clinical experience. We look forward to that the study will offer strong positive proof for acupuncture on aMCI.

